## Abstract

**Background:**

Screening and brief intervention in the emergency department (ED) has almost exclusively focused on individuals with alcohol-use problems. The early detection of mental health problems before problems become severe will enable early intervention and support which may improve health and prevent further deterioration. The main aim of this pilot study is to provide evidence of the acceptance of a telephone intervention aimed at ED attendees with moderate or high psychological distress. This will be determined by recruitment rates, retention rates and participant satisfaction with the intervention. Secondary outcomes include whether socio-demographic variables have an impact on retention rates, and whether the intervention had any impact on psychological distress.

**Methods/Design:**

This study will be a single-site pragmatic randomised controlled pilot study. Consenting ED attendees will be screened with the Kessler Psychological Distress Scales (K10). There will be three arms to the study: a moderate/high psychological distress group with or without intervention, and a low psychological distress group. Those with severe psychological distress will be excluded. All included participants will be followed-up at 1, 3, 6 and 12 months post-recruitment. Retention rates will be determined by successful completion of surveys at the follow-up time-points. Psychological distress will be measured by the K10 at all follow-up time-points.

**Discussion:**

This study will provide information regarding the potential for screening and recruitment at an opportunistic hospital presentation. It will provide data for a future larger study with regard to participants accepting to be included in this study. Participant acceptability will be measured in terms of recruitment rates and retention rates measured by successful follow-ups over the following 12 months post-recruitment.

**Trial registration:**

Australian and New Zealand Clinical Trials Registry ACTRN12614000031662. Registered 10/01/2014.

## Background

Mental illness is a major public health issue due to morbidity and other associated costs [1]. However, there are also individuals who may be free from a diagnosable mental illness but who may not feel healthy and/or are functionally impaired [2]. These sub-threshold symptoms are significant due to their prevalence, clinical significance, costs and risk of progression to more severe symptoms [3]. The ED is a potentially effective setting to target these issues due to the high prevalence of mental health problems in attendees [4–9]. Detection of mental health problems and treatment seeking before problems become severe, may improve health and prevent further deterioration [10]. This is consistent with the recommendations from several Australian government reports and publications regarding mental health and its management [11, 12].

The World Health Organization (WHO) describes mental health as being more than an absence of a mental disorder. It is a state of well-being, where the individual flourishes and realises their own potential, can deal with normal life stressors, work productively and contribute to society where they live [13]. Mental health can therefore be described as a condition free from mental illness, whilst mental illness describes symptoms of insufficient mental health. In Australia, almost half of the adult population (7.3 million) will experience a mental illness at some point in their life, whilst 20 % (3.2 million) will experience a mental illness this year, the most common being depression and anxiety [14]. However, there are many people in the community who, despite being free from a diagnosable mental disorder, may be languishing and not leading productive and healthy lives [2]. In 2003, mental health disorders contributed to 13 % of the total disease burden in Australia [15], and its annual cost is approximately $20 billion due to loss of productivity and reduced workforce participation [16]. In a 12-month period, almost 12 % of the Australian adult population made use of services for mental health problems, and from this group, only 35 % met the criteria for a mental health disorder, and a small proportion (6.1 %) of people with no mental health disorder also made use of these mental health services [17]. This reveals that there are other indicators of need for mental health services rather than mental illness alone.

Although sub-threshold syndromes are less defined than diagnosable mental illness, they still pose serious problems from psychological distress, which can impair a person’s development, career and education opportunities and increases their risk of future mental illness [18, 19]. The Australian Bureau of Statistics (ABS) uses the K10 to determine levels of non-specific psychological stress in its population surveys. Studies involving the K10 reveal a strong association between very high levels of psychological distress and diagnosable mental illnesses such as anxiety and depression [20]. The ABS National Survey of Mental Health and Wellbeing 2007 revealed that 67 % of the population had low-level psychological distress, 21 % had a moderate level, 9 % had high level and 4 % had a very high level [14, 21]. The absence of mental illness does not necessarily mean the presence of flourishing mental health, and it is important to consider the risk of sub-threshold symptoms progressing from moderate symptoms to more severe disorders [3, 18]. The promotion and protection of mental health may be beneficial and more cost effective, rather than to alleviate mental illness [10].

Early interventions and the recognition of the spectrum of mental health issues including those with mild or moderate impact with high and low prevalence were identified as a key area for reform in Australia's 4th National Mental Health Strategy [11]. The National Report Card on Mental Health and Suicide Prevention [12] also states that increased access to timely and appropriate health services reduces the longer term need for crisis intervention. Consumers can access mental health services either through hospitalisation, residential care, outpatient services or community services. From the 12 % of the population who accessed mental health services, one-third consulted community-based providers, mainly general practitioners (GP) who generally managed problems such as anxiety, depression and sleep disturbances [22]. However, GPs may have limited time in their practice as well as limited training and experience with mental health disorders [23]. EDs also provide some mental health services, but usually for patients who have an urgent or semi-urgent need [24], and the number of people accessing mental health services through the ED is increasing. In 2011–12, from the total of 7.8 million [25] presentations to public EDs, there were 248,501 [24] mental health-related presentations, representing 3.2 % of all presentations. This is an increase from 2008–2009, when there were 172,000 [26] mental health presentations from a total of over 7.2 million [27] ED presentations, representing about 2.4 % of all ED presentations.

Some EDs in major hospitals have developed an increasingly important role in providing crisis services to patients with mental health issues [28], and it is considered an appropriate setting for the detection of mental health problems [29]. Considering that the ED has a high yield of attendees with mental health problems, and that in the community, 30 % of the adult population are currently experiencing moderate and high levels of psychological distress, the ED would seem an appropriate setting for the detection of mental health problems in a non-mental health treatment-seeking population. Screening and identification of ED attendees with moderate or high psychological distress and encouraging them to seek follow-up care and support may improve health outcomes, and further deterioration of symptoms may be prevented.

### Prevalence study

A single-site cross-sectional study (*n* = 708) was conducted in 2011 to establish the prevalence of mental health issues of ED attendees [30]. Several mental health measures were employed, including the K10. Our data revealed that only 18 participants (2.6 %) received a primary ICD diagnosis related to mental health whereas 10.1 % scored in the very high K10 distress category. We also included a question on our general demographic and general health survey asking whether patients had any “mental health issues?”, and almost 17 % of participants answered positively. Based on norm data from the Australian population and the observed K10 scores from our pilot study, we were able to calculate the probability of ED attendees having a mental health disorder [31]. Stratum-specific likelihood ratios were applied to the sample of the 708 attendees. It was found that 37 % of all participants may have had an actual mental health disorder, which is higher than the population norm. Our data also showed that almost 40 % of ED attendees were affected by moderate/high non-specific psychological stress (identified using K10) [30]. This latter group is our target sample for the proposed study (moderate/high psychological distress).

### Current evidence

#### Motivational interviewing

Motivational interviewing (MI) is a non-confrontational, client-centred, directed therapy, which prepares individuals to become more receptive to change by exploring dissonance in the perceived benefits and costs of behaviours [32–34]. MI was developed originally for the treatment of substance-use [32], and its central principle is that motivation to change should be elicited from people, not somehow imposed on them [35]. It is an approach used to help a client realise that they may have a problem, build commitment to treatment, increase their engagement in treatment and enables behaviour change. The stages of change model [36] has proved useful for the understanding and conduct of an MI session. All change is preceded by some degree of ambivalence [35]; however, MI is particularly useful for working with clients who are ambivalent, resistant or reluctant to change [32, 37].

In the ED, MI has been shown to be effective in reducing alcohol consumption [38–43]. There are several studies which use MI as a pre-treatment to encourage treatment-seeking behaviours and therapy engagement. These studies have been set in an inpatient environment [44, 45], medical centres for veterans [46, 47], specialist outpatient clinics [48, 49] and a university psychology clinic [50]. All studies delivered the MI face-to-face, except for Seal et al. (2012) and Zinjani et al. (2008) which delivered the MI by telephone. The studies have demonstrated that participants randomised to MI pre-treatment had an increased attendance to psychiatric appointments. MI as a pre-treatment has also been shown to help reduce symptoms of worry [51] and fear [48]. The inclusion of MI to treatment strategies has benefits; however, efficacy has only been demonstrated on patients with diagnosed mental illness. Only one other study has been found which focused on participants with mild and moderate distress [10]. This study did not use MI but acceptance and commitment therapy and mindfulness to promote positive mental health. The authors stated that they used clinical judgement to identify patients and did not document whether they also used a screening tool. So far, we have found no studies which focus exclusively on MI with a sample with lower severity mental health problems.

The proposed pilot study focuses primarily on participants with moderate or high levels of psychological distress (identified by the K10) due to the high prevalence and excludes those with very high levels of psychological distress as this may indicate a pre-existing mental health disorder [20]. The purpose of the MI is to promote early intervention and to motivate participants to seek assistance for psychological distress. This study will also trial the provision of telephone MI which has been shown to be effective in samples with severe mental illness [46, 47] and alcohol studies based in the ED [42, 43]. In summary, there is extensive evidence of the effectiveness of brief intervention (MI) in the ED for alcohol-related samples, but it is relatively untested in mental health populations.

#### Aim

The main aim of this pilot study is to provide information for the planning of a future larger trial. The socio-demographic characteristics of participants and their relationship with recruitment rates and attrition rates will be assessed. Satisfaction with the intervention will also be assessed.

Secondary aims are to assess whether the telephone intervention has an effect on psychological distress levels and to determine if the K10 is a suitable method of screening and monitoring psychological distress. This is an unfunded PhD study which will inform the viability of applying for a substantive grant for a larger randomised controlled trial (RCT) with an economic evaluation.

## Methods/Design

Pragmatic randomised controlled pilot study.

### Ethical approval

Ethical approval for this study has been provided by the Human Research Ethics Committee from Metro North Hospital and Health Service (ref: HREC/13/QPCH/244) and the Australian Catholic University Human Research Ethics Committee (ref: 2013 294Q).

### Participants

All adult patients presenting to the ED of a public hospital during the specified data collection period will be screened to participate in the study. Those who meet the screening criteria and consent to participate in the study will be able to enter the pilot RCT.

Based on psychological distress assessment, consenting ED patients will be categorised into three initial groups; those with:Moderate or high psychological distressLow psychological distressVery high psychological distress

Subsequently, group 1 will be randomly allocated to receive either the MI or usual care (usual care does not involve MI). A randomised sample of participants which report low psychological distress will form group 2 to represent a “low-stress” population control group. The inclusion of a “low-stress” control group will allow for further assessment of recruitment strategies and retention of participants. Group 3 will be excluded from the study (but will be provided with advice to contact a health professional). Thus, there will be three arms to the study (see Table 1).

**Table 1 Tab1:** Randomisation of groups

Condition 1		Intervention
Group 1	Moderate/high psychological distress	MI plus usual care
	Moderate/high psychological distress	Usual care
Group 2	Low psychological distress	Usual care

#### Inclusion criteria

Inclusion criteria will include all alert and orientated English-speaking adults (over 18 years of age) who present to ED. Those attendees who have moderate or high levels of non-specific psychological distress, identified by the K10 (score 16–29) and do not require hospital admission will be eligible to enter the RCT study arm. They will be randomly allocated to either the intervention or control groups. Of the remaining participants, those with low psychological distress (score 10–15) will be enrolled in the “low-stress” control group.

#### Exclusion criteria

Participants with very high K10 scores will be excluded from the study and will be given phone numbers of community mental health clinics. Other exclusions include ED attendees unable or unwilling to give consent or those unwilling to be contacted by telephone, people with a cognitive impairment or a learning disability, participants admitted to hospital as in-patients or already participating in mental health programmes. Participants will also be excluded if they are in police custody.

### Screening

All participants will be screened using the K10. The K10 has been used in WHO surveys, with over 200,000 participants across 26 countries, as well as US, Canadian and Australian surveys [52]. It is a self-report tool that was developed based on extensive psychometric analysis in a large general population sample and was derived from existing screening scales by applying item-response theory to identify items that produced maximal discrimination of respondents at the 90–99th percentile, with a focus on severe mental illness [53, 54]. The resulting scale produced high discrimination scores between community and non-community cases of Diagnostic and Statistical Manual of Mental Disorders (DSM)-defined psychiatric disorders and had excellent discrimination in severe cases. The purpose of the screening scales is to screen for broadly defined mental disorders rather than for one particular diagnosis [53].

The K10 requires respondents to identify the frequency of symptoms of psychological distress within the past 30 days and focuses on anxiety and depressive states. It comprises four questions regarding anxiety, which focus on agitation and nervousness, and six questions about fatigue and negative effects. Each item is scored using a 5-point scale, ranging from 1 (none of the time) to 5 (all of the time), that defines behavioural, emotional, cognitive and psychological manifestations [55]. Participants categorised with low distress (score 10–15) are likely to be well. Those with moderate distress (score 16–21) are likely to have a mild mental health disorder, whilst those with high distress (score 22–29) are likely to have a moderate mental health disorder. Those scoring very highly (score 30–50) are likely to have a severe mental disorder [21]. There is a strong association between very high K10 scores and a current Composite International Diagnostic Interview (CIDI) diagnosis of anxiety and affective disorders and a lesser but still significant association between other mental health categories or the presence of any current mental disorder [20].

It could be argued that people coming into the ED would have higher distress scores due to the nature of their presentation. However, the K10 is assessing psychological distress over a 30-day period and not distress experienced on the day of presentation to ED or the few days immediately prior.

### Intervention

In this study, the MI will be used to encourage and motivate study participants to seek and obtain further assistance for their psychological needs. The overall spirit of MI is described as collaborative and evocative, and honours patient autonomy. A MI follows four guiding principles: resisting the fighting reflex, understanding and exploring the patient's own motivations, listening with empathy and empowering the patient, and encouraging hope and optimism [56]. The MI intervention has been designed to be pragmatic in that it will be tailored to each participant’s individual circumstances and needs.

Following recruitment, all participants will be provided with standard care, i.e. usual care from their ED attendance. Participants who are randomised into the intervention arm will receive an initial MI, delivered by telephone interview 48–96 h after their ED attendance, with up to three additional MIs by telephone during the following 2 weeks. Each MI is expected to last up to 60 min (a total of not more than 4 h for each study participant).

### Follow-up

For all study participants, longitudinal follow-up will occur at 1, 3, 6 and 12 months by telephone interview. The purpose of a 12-month follow-up is to ensure the usefulness of longitudinal data by measuring the impact of the intervention over time [57]. We also want to track the natural course of mental health from all participants. The primary goal of using the K10 at each follow-up time-point is to measure changes in psychological distress over 12 months and to be able to compare data with other studies.

### Outcomes

The main outcomesrecruitment rates as a percentage of eligible participantsattrition rates by measuring the completion of follow-up dataparticipant satisfaction by measuring whether the intervention is acceptable to the participants

Secondary outcomesmeasurement of the demographic characteristics of participants recruited to each arm such as: age, gender and education to determine inequities in retention ratesdetermining whether the intervention had an effect on K10 scores

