### Recruitment and randomisation

#### Recruitment

All adult attendees who present to the participating ED and meet the inclusion criteria will be eligible to enter the study. Recruitment of study participants will occur in the ED by a research assistant (RA), which will ensure that the existing staffing levels at the ED research site are not affected. Recruitment will occur at the time of the patient’s presentation to ED, with due consideration given to their particular circumstances. Those who are indisposed, severely injured or severely distressed due to their injuries may not be approached; in such circumstances, guidance will be sought from attending ED staff on an individual basis.

Each potential participant will be provided with an information letter by a researcher, explaining the study. Those who agree to participate will be required to provide written consent.

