#### Randomisation

Attendees who have moderate or high psychological distress will be randomised into intervention and control arms. Those with low psychological distress will be randomly selected (simple randomisation) to form a low distress comparison group for the purpose of measuring retention rates at follow-up and changes in K10 scores over time.

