#### Baseline

At recruitment, all consenting participants will be screened at time-point-a (T1a) and either included or excluded depending on K10 scores. Time-point-b (T1b) will commence post-screening, and data will then be collected from all eligible participants. Other data (such as primary ED diagnosis) will be collected from patient’s medical records.

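### The recruitment rate, a main outcome, has conflicting denominators: one reading drops refusers, and the aim linking recruitment to socio-demographics has no stated data on them

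*Protocol article*

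**What the plan says.** All references are to the protocol article.

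- **Outcomes:** the first main outcome is recruitment "rates as a percentage of eligible" participants. The Abstract uses recruitment rates, with retention and satisfaction, to judge acceptance of the telephone intervention.
- **Exclusion criteria:** "Other exclusions include ED attendees unable or unwilling to give consent or those unwilling to be contacted by telephone".
- **Baseline (under Measures):** "all consenting participants will be screened at time-point-a (T1a) and either included or excluded depending on K10 scores". The same section then uses the word eligible for those who remain, and collects the T1b data from them.
- **Inclusion criteria:** attendees with moderate or high distress "identified by the K10 (score 16–29) and do not require hospital admission will be eligible to enter the RCT study arm". Low scorers (10–15) are to be enrolled as the low-stress control group.
- **Recruitment:** "All adult attendees who present to the participating ED and meet the inclusion criteria will be eligible to enter the study". Information and written consent come after that.
- **Participants and Randomisation:** the low-distress group is a random selection from those who score low.
- **Aim:** "The socio-demographic characteristics of participants and their relationship with recruitment rates and attrition rates will be assessed".
- **Table 2:** demographics are not collected at screening (T1a), only at baseline (T1b).

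**The concern.** A recruitment rate measures acceptance only if people who could have entered and declined are in the denominator. Here unwillingness to consent or to take telephone calls is itself an exclusion. A person who declines for either reason can therefore be classed as ineligible and disappear from the rate. Declining telephone contact is direct evidence on whether a telephone intervention is acceptable, so that loss matters.

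The order of steps adds a second problem. Eligibility for any arm needs a K10 score, and only consenting people have one.

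The pilot exists to plan a larger trial. A rate near 100% that arises from the definition could lead that trial to underestimate how many attendees it must approach. The aim of relating socio-demographics to recruitment also needs a comparison between recruited and non-recruited people, and the stated data collection does not supply one for refusers.

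**Working it through.** The article states no recruitment-rate figure or target, so there is none to reproduce. The sample size of 30 per arm is taken from an audit median. The check follows the order of steps and then illustrates the size.

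**1. Order of steps.** Approach, then consent, then K10 (T1a), then inclusion or exclusion, then T1b data. A refuser stops at the second step, with no K10 score and no demographic form.

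**2. Two meanings of eligible.**
- *Exclusion criteria with Baseline:* eligible means willing, screened and in the K10 range. All such people with scores of 16–29 who are not admitted go on to randomisation, so recruited/eligible is near 100%. It falls short only if someone withdraws between the K10 and allocation.
- *Recruitment section:* eligible means meeting the inclusion criteria, with willingness not mentioned. Refusers stay in, but whether they would have scored 16–29 is unknown.

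**3. Illustration for the moderate/high group.** Inputs: 2 × 30 = 60 randomised (Sample size); about 40% moderate/high (Prevalence study). Assumptions: consent rate *c*, which the article does not give, between 30% and 90%; consent the same at all distress levels; everyone approached meets the basic criteria.

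Consenters screened = 60/0.40 = 150. Approached = 150/*c*. People with K10 16–29 among those approached = 60/*c*.

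| Assumed consent | Approached | Refusers | Refusers out | Refusers in, K10 16–29 only (95% Wilson CI) | All approached |
|---|---|---|---|---|---|
| 30% | 500 | 350 | 60/60 = 100% | 60/200 = 30% (24–37) | 60/500 = 12% |
| 50% | 300 | 150 | 60/60 = 100% | 60/120 = 50% (41–59) | 60/300 = 20% |
| 70% | 214 | 64 | 60/60 = 100% | 60/86 = 70% (59–79) | 60/214 = 28% |
| 90% | 167 | 17 | 60/60 = 100% | 60/67 = 90% (80–95) | 60/167 = 36% |

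The fourth column does not move with consent. The fifth does, but its denominator can be had only by assuming a K10 distribution for refusers. The last needs no K10 for refusers, but it mixes refusal with K10 ineligibility. That is why the stages have to be reported separately.

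**4. Low-distress group.** If 30 are randomly selected, recruited/eligible = 30/(number scoring 10–15), which is a sampling fraction. The article does not give it. Two illustrations, both assuming that screening stops once 60 are randomised:
- Prevalence study: low share = 1 − 0.40 − 0.101 = 0.499; 150 × 0.499 ≈ 75; 30/75 = 40%.
- National survey figures in the Background (67% low, 21% + 9% = 30% moderate/high): 60/0.30 = 200 screened; 200 × 0.67 = 134; 30/134 = 22%.

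If low scorers are simply enrolled until 30 are reached, as the Inclusion criteria suggest, the figure is again near 100%. None of these values measures willingness.

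**5. Socio-demographics and recruitment.** Demographics are taken at T1b, after consent and K10. The secondary outcome covers the characteristics of those recruited and concerns retention. Data analysis describes those lost to follow-up, not those never recruited. No collection is stated for refusers or for those excluded on K10.

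**The case against.** The strongest reply is that the article never says the rate uses a post-consent denominator. The Recruitment section puts eligibility before consent, the Participants section treats meeting the criteria and consenting as separate conditions, and the Discussion in the Abstract speaks of participants accepting inclusion. This stands in part. A reader might infer that refusers are definitely out of the denominator, and the documents do not support that. They support a conflict between the Exclusion criteria and the Recruitment section.

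It is also fair that the K10 status of refusers is unknowable under any definition when screening follows consent. Separate stages do not recover it. They only stop it from being hidden inside one ratio.

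Other strong readings fail too:

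- *The low-group rate is capped at 40%.* That figure rests on assumed counts and on random selection, which the Inclusion criteria do not repeat. The article does not say that the rate will be computed by group.
- *No demographics exist for anyone not recruited.* T1b data come from all eligible participants, which may include low scorers who were not selected. The gap is clear only for refusers and for those excluded on K10.
- *The study cannot show acceptability.* Retention and satisfaction are also main outcomes and bear on it directly.

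Finally, one may say that a condensed article leaves recruitment flow to a fuller document. That would answer an omission. It does not answer two stated meanings of the word on which a main outcome depends.

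**Conclusion.** The concern holds as a conflict of definitions. Under the Exclusion criteria and Baseline sections, the moderate/high recruitment rate is near 100% regardless of acceptance. Under the Recruitment section refusers are kept, but their K10 eligibility is unknown. With the illustrative inputs, the same trial could report 100%, or anything from 30% to 90% with refusers counted. Those figures rest on an assumed consent range, about 40% prevalence and equal consent across distress levels. The conflict itself needs no assumption.

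For the low-distress group the point is conditional: if selection is random, the ratio is a sampling fraction of unstated size. The socio-demographic aim lacks stated data for refusers and for those excluded on K10.

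The defect is confined to the recruitment rate and the recruitment part of that aim. It does not touch the sample size, the random allocation or the other two main outcomes. Recruitment closed in May 2015 (Trial status), so what can still change is definition and reporting. That is worth doing, because it alters a main outcome meant to plan the next trial.

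**What to change.** Reconcile the Exclusion criteria with the Recruitment section. For this outcome, count refusal of consent or of telephone contact as non-recruitment. Then report three proportions, each with a 95% confidence interval:

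1. consented / approached attendees who meet the criteria other than willingness;
2. K10 16–29, and separately K10 10–15 / screened;
3. entered / K10-eligible and offered entry, with only randomly selected people in the low-distress denominator.

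State also whether low scorers were randomly selected or all enrolled, since the sections differ.

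The article mentions no log of approaches, so the first proportion depends on whether approach counts were kept. If they were not, the report should say that consent among those approached cannot be given. If approach counts with age and sex, or aggregate ED register data for the sampled 5-hour blocks, are available, compare age and sex of recruited and non-recruited attendees. Otherwise remove recruitment rates from the socio-demographic aim and keep attrition.

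Cost: wording, some extra tabulation, possibly an ethics note for aggregate data, and a less favourable recruitment figure.
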